### Sample size

There will be one primary comparison between the two study arms (SMC vs SCC) and a secondary comparison between those classified as DYS across study arms, anticipating that approximately half of each study arm will be classified as DYS. Based on the previous study [17], to detect a difference in the number of days with pain over 12 months [17] between the two main study arms corresponding to a medium Cohen’s effect size of 0.5, with an α-level of 0.05, power of 0.80, a sample consisting of 90 patients per arm would be required. Given that our study includes 2 arms and to account for potential dropouts (20%), our goal will be to recruit 220 patients [52]. Therefore, 15 clinicians will be recruited to collect data from 15 patients each.

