### Safety monitoring

A Data and Safety Monitoring Board (DSMB) will monitor participant safety, data quality, and the progress of the trial. The DSMB includes a physiotherapist with expertise in patient safety and two chiropractors: one with expertise in clinical trials and one with expertise in patient safety. The DSMB will communicate frequently via email throughout the study, formally meet every 6 months, and monitor data quality and adverse events. While there is no pre-planned auditing of the trial, the institutional research ethics board may perform post-approval monitoring and auditing of the trial conduct.

Based on the literature, for both groups, we anticipate only mild adverse events (AEs) commonly reported following chiropractic treatments, such as mild discomfort/pain and stiffness [62, 63]. All patient follow-up questionnaires will include specific questions about AEs. If an AE is reported, the principal investigators will be notified immediately via email for documentation and reporting in the final manuscript. Upon notification, at least one of the principal investigators will review the AE report by accessing the participant’s response on REDCap and identify the type of AE and severity based on pre-defined criteria [64]. If any serious adverse event (SAE) that interferes with study protocol compliance is identified, it will be reported to the ethics board, the respective chiropractor will be notified, and patients will be instructed to discontinue the study.

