### Provisions for post-trial care

As no adverse events beyond normal transient mild discomfort/pain are expected, no follow-up plans will be included in this study.

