### Data analysis plan

#### Primary outcome

An intention-to-treat protocol will be used, and estimates will be reported with arithmetic means and 95% confidence intervals. The primary outcome (number of days with activity-limiting pain) will be analyzed similar to Eklund et al. (2018,2019) [17, 48]. The number of days with activity-limiting pain will be modeled using generalized estimating equations (GEE) linear regression, using appropriate correlation structure and robust variance estimator. Terms for study arm, time, and study arm by time interaction will be included. A term for MC candidate (yes or no) will be added to this model to investigate stratification and its relationship to outcomes further.

Following a previous study that conducted a similar analysis [16], cost-effectiveness will be investigated both from the health care and societal perspectives. In the health care perspective only costs directly associated with the intervention will be included whereas in the societal perspective all available costs, direct and indirect modeled production loss costs, will be used. Direct medical costs considered in the study are treatment costs (treatment fee) and time loss during treatment and travel (an average time for travel is estimated and added to an average patient visit time). Indirect costs, such as production loss, will be estimated using the human capital approach, where lost time is valued using the hourly wage [65]. Since the data collection is performed between 2023 and 2025, all costs will be adjusted for inflation using a 3 to 5% inflation rate, with the baseline year of the study as a base year [66] and calculated in CAD$. Intervention effectiveness will be estimated by the primary outcome “number of days with a bothersome spinal pain” and self-rated health (EQ5D) as a secondary outcome. The results will be reported as cost-effectiveness planes, cost acceptability curves, and incremental cost-effectiveness ratios (ICER) where the extra cost per extra unit of health effect will be estimated for days with bothersome pain and quality-adjusted life years (QALYs). No interim analyses are planned for this study.

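### The rule for serious adverse events tells patients to leave the study without separating care from outcome collection, which sits badly with the intention-to-treat analysis (minor)

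*Protocol article*

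**What the plan says.** All places are in the protocol article.

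- **Safety monitoring, the rule.** "If any serious adverse event (SAE) that interferes with study protocol compliance is identified, it will be reported to the ethics board"; the chiropractor is then told, and "patients will be instructed to discontinue the study". The object is the study as a whole. Nothing says whether SMS or questionnaire follow-up goes on.
- **Safety monitoring, harms capture.** Every patient follow-up questionnaire asks about adverse events. Reported events go to the principal investigators. A Data and Safety Monitoring Board (DSMB) monitors adverse events, with no restriction to those affecting compliance.
- **Safety monitoring, expected frequency.** No SAE rate is given: "we anticipate only mild adverse events (AEs) commonly reported following chiropractic treatments".
- **Data collection.** The primary outcome comes from automated SMS questions every 2 weeks for 12 months, and the questionnaires go out by e-mail.
- **Data analysis plan, Primary outcome.** "An intention-to-treat protocol will be used". The model is a linear GEE with robust variance and terms for arm, time and their interaction.
- **Sample size.** A 20% allowance for dropout from all causes, with a recruitment goal of 220.

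**The concern.** Intention to treat asks for two things: patients are analysed in the arm to which they were allocated, and they are followed for outcome whatever happens to their care. The SAE rule works against the second. It is a stated instruction, not an omission, and it is triggered by a post-randomisation event that may be related to treatment or outcome.

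The loss is also avoidable. The SMS and e-mail systems run without clinic visits, so a patient whose care changes can still report days with activity-limiting pain.

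The trigger might act unequally. The intervention arm has defined pathways (Stratified MC), while the control arm follows the clinician's judgment (Standard chiropractic care). The same event could therefore be seen as interfering with compliance more readily in one arm. That is an inference; the article does not say so.

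Harms data are affected too. Leaving the study ends the adverse-event questions for a patient who has just had an SAE, although Dissemination plans commits to CONSORT-Harms reporting.

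A related wording point is that the only stated route to the ethics board covers SAEs that interfere with compliance. The route for an SAE that does not interfere is unclear.

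**Working it through.** **1. Passages side by side.** Safety monitoring sends a defined group of randomised patients out of the study. Primary outcome promises an intention-to-treat analysis of an outcome collected fortnightly over 12 months. Both can be carried out together only if leaving means leaving study care while reporting continues, and the text does not say that. Provisions for post-trial care adds that "no follow-up plans will be included in this study". That section concerns care after the trial, so it neither supplies nor forbids SMS follow-up within the 12 months.

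**2. Size.** The plan gives no figure for losses under this rule, so there is none to reproduce. What follows is an illustration.

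Inputs from the article: reports every 2 weeks for 12 months, so about 26; linear GEE with arm, time and arm-by-time.

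Assumptions: SAE rates p1 and p0 in the two arms; after the SAE a patient's reports are Δ = 3 days per fortnight higher and are all lost; onset is evenly spread over report indices 2 to 25 (counting from 0), mean 13.5, so on average L = 26 − 13.5 = 12.5 reports are lost; patient and residual SD are both 2 days.

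The unseen excess enters the true arm difference but not the observed one, so

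bias ≈ −(p1 − p0) × L × Δ days per year.

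This was compared with a simulation of the GEE (12 runs of 1,500 patients), setting the GEE estimate against the estimate had everyone been followed. Standard errors are in brackets.

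| p1 v p0 | Formula | GEE, independence | GEE, exchangeable |
|---|---|---|---|
| 1% v 1% | 0 × 12.5 × 3 = 0 | −0.01 (0.09) | −0.05 (0.06) |
| 2% v 0% | −0.02 × 12.5 × 3 = −0.75 | −0.83 (0.08) | −0.70 (0.06) |
| 5% v 2% | −0.03 × 12.5 × 3 = −1.13 | −0.89 (0.10) | −1.06 (0.08) |

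The largest gap between formula and simulation is 0.24 days, about two and a half standard errors with only 12 runs, so the two agree broadly. The sign favours the arm with more SAEs. The bias scales in proportion to each of the three factors.

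**3. When the bias disappears.** With the same unequal loss by arm but no link between loss and outcome, the simulated bias was within ±0.1 day. With equal rates it was about 0 even when loss was related to the outcome. Both conditions are needed.

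**4. Numbers of patients.** With 220 / 2 = 110 per arm, rates of 5% and 2% mean 110 × 0.05 = 5.5 and 110 × 0.02 = 2.2 patients, about 8 in all. The dropout allowance is 220 × 0.20 = 44. The issue is bias, not power.

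**The case against.** The strongest reply is that the phrase may loosely mean stopping study care, that a journal article condenses the full protocol, and that very few patients will meet the trigger. All three are fair, and they are why the point is minor. They do not remove it. The published sentence is an instruction that site staff could follow literally, and nothing else in the article limits it.

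Two stronger readings are tempting.

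- *A reader might infer that these patients cannot be analysed as randomised.* The documents do not support that. They stay in their allocated arm and contribute every report made before exit. Later data are lost, but the allocation principle is not broken.
- *A reader might infer that the planned GEE is valid only if loss is completely random, and that imputation or a mixed model is therefore needed.* That is too absolute. Loss that depends on arm and time is allowed, because both are in the model, and the simulation bears this out. Loss driven by unseen outcomes would also bias a likelihood model or imputation from earlier reports, so it is not a fault of GEE. Missing-data handling may properly sit in a statistical analysis plan that is not shown.

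On safety, the objector can also say that every reported adverse event is reviewed by a principal investigator and documented for the final manuscript, and that the DSMB monitors adverse events in general. That stands: the article does not show that SAEs go unreviewed. What is left is an unclear route to the ethics board.

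**Conclusion.** The point holds as a minor inconsistency. As worded, Safety monitoring ends outcome and adverse-event follow-up for some randomised patients because of a post-randomisation event, and this must be reconciled with the intention-to-treat statement in the analysis plan.

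The likely bias is about 1 day per year or less. That rests on assumed SAE rates of up to 5%, an assumed worsening of 3 days per fortnight, and loss that both differs by arm and relates to the unseen outcome. If either of the last two conditions fails, the bias is about nil. The article gives no SAE rate, so these figures are illustrative.

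A reader might size the problem from the 20% dropout allowance. That figure covers loss from every cause and does not measure this rule. Nor does the article show that the affected patients would have the worst pain outcomes: an SAE that interferes with compliance need not involve the spine.

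**What to change.** - **Follow-up.** In Safety monitoring, separate care from data. State that, whatever is decided about care after an SAE, SMS and questionnaire follow-up (including the adverse-event questions) continues for all randomised patients unless they withdraw consent to data collection. In the analysis plan, state that reports collected after such an event are included in the allocated arm.
- **SAE reporting.** Reconcile the sentence that ties ethics-board reporting to interference with compliance with the DSMB's monitoring of adverse events generally, so that the route for an SAE that does not affect compliance is explicit.

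Neither change sets a clinical rule. The cost is two or three sentences, slight extra follow-up and some paperwork. If sites already continue follow-up, this is a clarification; if not, it changes trial procedures and would go through the article's own amendment process. Recruitment is planned to May 2026 and data collection to July 2027, so on that timetable the earlier the change is made, the more patients it covers.

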### Provisions for post-trial care

As no adverse events beyond normal transient mild discomfort/pain are expected, no follow-up plans will be included in this study.

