### Data collection

The automated SMS track, via Twilio System, will be used to collect SMS, and REDCap will be used to collect electronic questionnaire data. Each participating clinician will complete an initial questionnaire (Questionnaire 0-clinician) to record their individual characteristics.

Upon Questionnaire 0-patient completion, participating patients will be automatically registered in the Twilio system, given a confidential study ID linked to the clinician from which they are receiving treatment, and automatically scheduled to receive 3 questions via SMS every 2 weeks for 12 months. The follow-up questionnaires (Questionnaire 1–4) will be automatically sent via e-mail to both participating patients and clinicians at 3 weeks, 3, 6, and 12 months, respectively.

Data collection will be monitored daily in real-time, and contact with participating patients and clinicians will ensure high response rates. Specifically, in case of email delivery notification from REDCap or identification of incomplete questionnaires, email reminders will be sent to participating patients and clinicians.

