### Concomitant care

Given that this is a pragmatic study, the concomitant use of other treatments and interventions will not be restricted during the study. The intervention will not interfere with other regular medical care and medications, which will continue as usual during the study.

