### Protocol amendments

Any modifications to the protocol which may impact the conduct of the trial, potential benefit of patients or may affect patient safety, including changes of study objectives, trial design, participant population, sample sizes, trial procedures, statistical analyses, or significant administrative aspects will require a formal amendment to the protocol. Such amendments will be agreed upon by the research team and, if needed, approved by the local Research Ethics Board. Administrative changes of the protocol (e.g., minor corrections and/or clarifications) that have no effect on how the trial is conducted will be agreed upon by the research team and documented.

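### No follow-up is planned after the last study contact, and no exception is made for a serious adverse event that is still unresolved then

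*Protocol article*

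**What the plan says.** The section Provisions for post-trial care consists of one sentence: "As no adverse events beyond normal transient mild discomfort/pain are expected, no follow-up plans will be included in this study". It gives that single reason and no exception.

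Safety monitoring starts from the same expectation: "we anticipate only mild adverse events (AEs) commonly reported following chiropractic treatments, such as mild discomfort/pain and stiffness". It then provides for events outside it. A principal investigator reviews each reported event to "identify the type of AE and severity based on pre-defined criteria". For serious events it says: "If any serious adverse event (SAE) that interferes with study protocol compliance is identified, it will be reported to the ethics board", and continues: "the respective chiropractor will be notified, and patients will be instructed to discontinue the study".

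Adverse events are asked about in every patient follow-up questionnaire. Under Data collection, these questionnaires "will be automatically sent via e-mail to both participating patients and clinicians at 3 weeks, 3, 6, and 12 months, respectively". The 12-month questionnaire is thus the last scheduled adverse event query.

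Other provisions bear on the point. A Data and Safety Monitoring Board monitors adverse events and formally meets every 6 months (Safety monitoring). On usual care, the article says: "The intervention will not interfere with other regular medical care and medications, which will continue as usual during the study" (Concomitant care). Dissemination plans commits the publications to CONSORT with its harms extension.

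**The concern.** The decision not to plan follow-up rests on events being mild and short-lived. A patient with a serious event is the one for whom that reasoning fails and who most needs someone to ask how the event ended. The article makes no exception for this patient, although the section just before it describes such an event and the steps to take.

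Two things are at stake. One is patient safety: the trial may lose sight of a participant whose serious event is still open. The other is harms reporting: the trial could report a serious event without knowing whether it resolved, continued or left lasting effects, which would make the promised harms report less informative. Effect estimation is not at stake.

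**Working it through.** No figure in the plan needs to be reproduced, and the point depends on no alpha, power, effect size or sample size. The check sets the provisions side by side and follows an open serious event through them.

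1. **What is expected and what is foreseen.** Safety monitoring anticipates mild events only. The same section has severity graded and lays down actions for an SAE that interferes with compliance. The expectation is therefore not treated as a certainty. Provisions for post-trial care rests on that expectation alone.

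2. **Event open at 12 months.** Adverse event queries are scheduled at 3 weeks and at 3, 6 and 12 months. An SAE first reported at 12 months, or still unresolved then, has no later scheduled query, and the post-trial section plans no follow-up. This holds however the instruction to discontinue is read.

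3. **Event that leads to discontinuation before 12 months.** Two readings are possible.
   - The patient stops study treatment and the questionnaires continue. No scheduled query is then lost, and only the situation in step 2 remains.
   - The patient stops the questionnaires as well. There is then no stated contact after discontinuation.

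   The article does not say which is meant. The second reading is therefore a condition of this part of the point and not a finding.

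4. **Do other provisions supply the contact?**
   - Investigator review takes place when an event is reported. Its stated purpose is documentation and reporting.
   - Notifying the chiropractor is a partial clinical hand-off. No return of the outcome to the trial is stated.
   - The ethics board report and the monitoring board give oversight. Neither is stated as a contact with the patient after the last visit or questionnaire.
   - Usual medical care helps the patient but returns no outcome to the trial.
   - The harms extension governs reporting, and the article states no collection of outcomes after exit.

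   None of these is stated as a contact that establishes how an unresolved SAE ended.

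5. **Workload of an exception.** At one contact per qualifying event, extra contacts = 1 × number of qualifying events. If the plan's expectation holds, this is 1 × 0 = 0. The article gives no SAE rate and none is assumed here. An event that is still open at the first contact could need more than one.

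6. **Room in the timeline.** Project timeline has recruitment running to May 2026 and data collection ending in July 2027. Take the latest case, a patient enrolled on 31 May 2026, with 12 months counted from enrolment (an assumption). The last questionnaire falls due on 31 May 2027. From then to 1 July 2027 is 30 + 1 = 31 days, and to 31 July 2027 it is 30 + 31 = 61 days. Patients enrolled earlier have longer.

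**The case against.** The strongest reply is that the sentence stands under a post-trial care heading and most naturally means that no routine programme of care or contact is planned. It does not forbid an investigator from contacting a patient with an open serious event. This stands. A reader might infer that follow-up of a serious event is prohibited, but the text does not go that far. What remains is that the article takes a decision, gives its reason, and makes no exception where the reason fails.

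A second reply is that a patient told to discontinue during the 12 months falls under Safety monitoring and not under the post-trial section. That section does not say that questionnaires stop, and the intention-to-treat approach fits at least as well with continued collection. The full protocol, which is not shown, may also hold more on handling SAEs during the trial. This stands too. A reader might be tempted to count the queries and weeks of observation lost after an early SAE. The documents do not support such a count, because it depends on a reading of the instruction to discontinue that is nowhere stated.

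A third reply is that the existing safeguards leave no such patient without care or oversight. This is correct as to care: the chiropractor is told, usual medical care goes on, and the ethics board and monitoring board are involved. It does not supply the missing item, which is a recorded outcome.

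Finally, extending the exception to events graded above mild relies on severity criteria taken from a cited source that is not shown. That part of the remedy can only be conditional.

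The reply that a journal article condenses the protocol does not dispose of the point. The article is not silent on post-trial follow-up; it states that there is none.

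**Conclusion.** The point holds in a limited form and is one to consider. The protocol article plans no follow-up after the trial on the strength of an expectation, and makes no exception for the serious event that its own safety section foresees. An SAE unresolved at the 12-month questionnaire has no stated contact to establish its outcome. The same applies at discontinuation only if discontinuation also ends the questionnaires, which the article leaves open.

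The number of patients affected is unknown and likely very small. If the plan's expectation holds, it is zero. The primary outcome, the sample size and the analysis are unaffected, and the safety queries during the 12 months stand as planned. The conclusion rests on the stated decision in Provisions for post-trial care. It does not rest on what the full protocol may say about handling SAEs while a patient is in the trial.

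**What to change.** Keep the decision to have no routine post-trial follow-up, and make two short changes.

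- **Provisions for post-trial care:** add that any SAE unresolved at the patient's last study contact gets a follow-up contact, for example through the existing REDCap and email system, and that its outcome (resolved, ongoing or lasting) is recorded and reported. Apply the same to any adverse event graded above mild, provided the pre-defined criteria allow that grade. Mild transient events need no extra contact. The trigger should be any SAE, not only one that interferes with compliance.
- **Safety monitoring:** clarify that a patient told to discontinue because of an SAE stops study treatment but is still asked about the outcome of that event, unless consent is withdrawn.

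The section Protocol amendments says that changes which may affect patient safety "will require a formal amendment to the protocol", so a short formal amendment is the route. The running cost is zero to a few extra contacts. The 31 to 61 days available in the latest case should normally be enough for a first contact. The database may close slightly later if an event is still open then.
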